#### Timing of analyses

We will analyze treatment effect when the last family has completed the post-assessment battery. We will start analyzing the follow-up data when the last family has completed the follow-up assessment.

#### For effects according to time-invariant assessments

For analyses of trajectories of change, we will employ mixed-effects regression analyses and growth curve analyses (for the pre, 3-, 6-, and 15-month data and PATH data).

#### For subgroup analyses

Descriptive statistics, general linear models (GLM), and multiple group analyses.

#### For associations of implementation quality and fidelity

Correlation, regression, and interactional models.

#### For predictors of treatment outcomes (other than treatment condition**)**

Structural equation models, regression, path modeling.

#### Level of significance to be used

In most analyses, a significance level of α = .05 will be used for main effects analyses, mediation models, growth curve models, and general models of association. We will use more stringent alpha levels in subsequent analyses in cases where many variables are entered into prediction models, to reduce the risk of Type 1 error.

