#### Top Problem Assessment (TPA)

Children and parents fill out a severity rating (on a scale of 0 to 4) of the top three problems the youth and parent independently identify as most important to them in separate structured pre-treatment interviews. Psychometric analyses of the TPA have shown strong reliability, validity, and sensitivity to change during treatment in earlier studies of MATCH in the US [23, 24]. The TPA is part of the PATH system and ratings are collected weekly during treatment.

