#### Behavior and Feelings Survey (BFS)

Children and parents fill out a 12-item measure of internalizing (six items; scores can range from 0 to 12), externalizing (six items; score range, 0–12), and total problems (12 items; score range, 0–24). This BFS was developed through psychometric testing of an item pool derived from the “top problems” identified by previous samples of clinically referred children and their parents. BFS scores show convergent and discriminant validity in relation to the appropriate scales of other child- and parent-report problem scales: the CBCL and YSR, the Strengths and Difficulties Questionnaire, and the Youth Outcome Questionnaire. The BFS is used with the PATH system, through which ratings can be collected weekly.

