#### The Achenbach System of Empirically Based Assessment (ASEBA; CBCL and YSR)

The child’s behavior and symptomology are assessed by multi-informant ratings from caregivers and children on the CBCL [1] and YSR [1], respectively. This family of measures is one of the most widely used to assess child and adolescent emotional and behavioral functioning and has been validated in numerous studies (e.g., [12]). The instruments assess a broad array of behavioral and emotional manifestations of psychopathology, yielding eight syndrome scales of which the broad band scales “Internalizing” and “Externalizing” will be of particular importance in this study. CBCL and YSR are administered at the pre-, post-, and follow-up assessments. Parents also complete the internalizing and externalizing sub-scales of the CBCL at the 3-, 6-, and 15-month assessment points (waves 2, 3, and 5).

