### Design and power

The trial is a randomized controlled effectiveness trial conducted in existing child and adolescent outpatient clinics in Norway. Participants are randomized within each site, following a computer-generated list with each participant having a 50% chance of being assigned to either group. The results of the randomization are provided to the clinic for each new case. The process is as follows:*Referral*: children and their families are referred to the participating clinics (primarily by either their general physician, head of the municipal child welfare agency, or community psychologist) for child symptoms of anxiety, depression, trauma-related problems and/or conduct problems. Children and families are assessed for eligibility for the study based on these referral reasons, and on whether they have significant symptom levels meeting study cut-offs at the time of screening (see item c and “Rationale for the use of cut-off scores” below)*Consent*: once found eligible at this stage, families are informed of the trial by the contact person at the clinic. If the family consents, their contact information is given to the Norwegian Center for Child Behavioral Development (NCCBD) which then registers the information and contacts the family to provide more information about the trial and to ask whether the family wants to participate. The family is informed briefly about the treatment options and that random assignment is involved. If the family agrees, a consent letter, along with a brief study description (including contact information of the study personnel), is sent to the family. The NCCBD then registers receipt of a signed consent from the family. A phone call is made to the family within a few days to make sure that they have received the letter in the mail. If the NCCBD has not received a signed consent within 2 weeks, another phone call is made to the family, to allow for questions and to urge interested families to sign and send in the consent form.*Pre-assessment and decisions about inclusion to the trial*: upon receipt of a signed consent form from the family, the pre-intervention assessment (wave 1) is sent out to the family This is done approximately 2 weeks prior to the date set for their first consultation at the clinic. A reminder is sent out to the family after 1 week, and is followed up by weekly phone calls if they have not submitted the completed assessment. The pre-intervention assessment, on which scores are based to assess eligibility to the trial, include the CBCL, YSR, KATE and if relevant (given the scores on the KATE), the child and parent version of CATS. Children between the ages of 8 and 11 years complete these questionnaires at the clinic together with a clinician. The family is eligible if the child’s scores are at or above clinical cut-off scores.*Further assessment by the clinics and setting the primary protocol*: the clinics receive the summary scores on the CBCL, YSR, KATE, and CATS from the NCCBD. In some cases, the clinics administer these questionnaires directly to the families as part of their routine, and in these cases, the NCCBD receives the results from the clinic(s), after collected consent. For children with T-scores above the cut-off, a therapist at the clinic conducts a TPA. Based on the result from these assessments, MATCH consultants make the decision about the child’s primary protocol to be tried first (primary problem area). MATCH consists of four treatment protocols, one for each problem area; anxiety, depression, trauma, and conduct problems*Randomization*: once inclusion to the study and primary protocol are determined, the family is randomized to either the MATCH condition or the TAU condition. Information about the outcome of the randomization procedure is then provided to the clinic. The outcome of the randomization then triggers two events: (1) the dates for the time-invariant assessment points (i.e., the 3-, 6-, and 15-month assessments) and (2) the clinics being alerted to inform the NCCBD of who the therapist for the family will be, along with their contact information*Registration in PATH*: families are then added to the PATH system a week prior to their first meeting with their appointed therapist. The families receive an email on the Sunday of each week asking the parent and the child (if they are over 8 years old) to fill out a questionnaire, consisting of the TPA and the BFS. The TPA and the BFS are collected weekly (or between each session) as part of the PATH system of user feedback

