#### Primary outcomes

CBCL/YSRCATSWeekly PATH scores: TPA and BFS (throughout treatment)Time in therapy

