#### The selection of participants to be included in the analyses

We will answer two important research questions: First, to answer the question of “Does MATCH work?” we will employ a per-protocol design; thus only those children and families who have gone through treatment will be included. Second, the question of whether “MATCH makes a difference in existing clinics” is best approached via an intention-to-treat design (ITT), in which all families randomized will be included in the analyses, regardless of whether they entered or completed treatment. Thus, we will analyze data using both ITT and per-protocol designs in an effort to answer these two overall questions.

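### Five unranked primary outcomes (about 12 to 15 comparisons) are tested mostly at .05 with no rule for which decides, giving roughly a 12–23% chance of a false result favouring MATCH against a nominal 2.5%.

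*Protocol article*

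**What the plan says.** Under Primary outcomes the article gives one flat list, run together in the extracted text: "CBCL/YSRCATSWeekly PATH scores: TPA and BFS (throughout treatment)Time in therapy". It states no lead outcome, order, composite or requirement that all must succeed.

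Several entries split further by scale and informant:

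- **CBCL and YSR:** the "broad band scales “Internalizing” and “Externalizing” will be of particular importance in this study", rated by caregivers on the CBCL and by the child on the YSR.
- **CATS:** Design and power refers to "the child and parent version of CATS".
- **TPA:** "Children and parents fill out a severity rating (on a scale of 0 to 4) of the top three problems".
- **BFS:** "Children and parents fill out a 12-item measure of internalizing", externalizing and total problems.

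The section on significance levels says: "In most analyses, a significance level of α = .05 will be used for main effects analyses, mediation models, growth curve models". The same section continues: "We will use more stringent alpha levels in subsequent analyses in cases where many variables are entered into prediction models". The sample size section plans 280 children to detect an effect size of 0.3 with power .80 at alpha .05, for the main effect. The section on who enters the analyses adds that "we will analyze data using both ITT and per-protocol designs". The Aims ask about CBCL, YSR and CATS at post-treatment and again at 1-year follow-up.

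**The concern.** The article does address Type 1 error, but the only stricter level it states applies to later prediction models. The primary comparisons, on which a claim for MATCH would rest, are left at the ordinary level.

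With an unranked primary list, a mixed set of results has no agreed reading. One favourable scale from one informant could be presented as a positive trial, and the same results could equally be called negative. The per-protocol analysis adds a second route, because the article assigns the question of whether MATCH works to that set. At stake is whether a significant primary result carries the 5% error rate that readers will attach to it.

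**Working it through.** **1. The plan's own figure.** With 140 per arm and d = 0.3, d·√(n/2) = 0.3 × √70 = 2.510.

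- One-sided .05: power = Φ(2.510 − 1.645) = 80.7%. Required total = 2 × 2(1.645 + 0.842)²/0.3², which rounds up to 276.
- Two-sided .05: power = Φ(2.510 − 1.960) = 70.9%. Required total is 350.
- Two-sided with baseline adjustment: 294 at an assumed correlation of 0.4 and 262 at 0.5.

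So 280 reproduces for one test, either one-sided or two-sided with an unstated covariate gain. It makes no allowance for several primary tests.

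**2. Count of primary comparisons at one stage.**

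| Outcome | Lower | Upper | Reason for the range |
|---|---|---|---|
| CBCL internalizing, externalizing | 2 | 2 | |
| YSR internalizing, externalizing | 2 | 2 | |
| CATS | 1 | 2 | after T1 the child completes it only if a new trauma is reported |
| TPA, parent and child | 2 | 2 | |
| BFS, parent and child | 4 | 6 | the total is the sum of the other two scores |
| Time in therapy | 1 | 1 | |
| **Sum** | **12** | **15** | |

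The 1-year comparisons of CBCL, YSR and CATS add 5 or 6, giving 17 to 21, before any per-protocol repeat.

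**3. Chance of at least one p < .05 under no effect.** For k independent tests it is 1 − 0.95^k in either direction and 1 − 0.975^k favouring MATCH. For k = 15: 1 − 0.95^15 = 0.537 and 1 − 0.975^15 = 0.316. For correlated tests the model is Z_j = √ρ·F + √(1−ρ)·E_j, with F and E_j independent standard normal and a threshold of 1.96. The values of ρ are assumptions. Each cell gives either direction / favouring MATCH, in %.

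| Tests | ρ = 0 | 0.3 | 0.5 | 0.7 | 0.9 |
|---|---|---|---|---|---|
| 15 | 54 / 32 | 46 / 23 | 36 / 18 | 26 / 13 | 14 / 7 |
| 12 | 46 / 26 | 40 / 20 | 32 / 16 | 23 / 12 | 13 / 7 |
| 5 (one per listed outcome) | 23 / 12 | 21 / 11 | 18 / 9 | 15 / 7 | 10 / 5 |

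The single-test reference is 5 / 2.5. With 21 tests, at ρ = 0.3, 0.5 and 0.7, the rates are 55, 43 and 30% in either direction and 29, 22 and 15% favouring MATCH.

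**4. Price of adjusting instead of choosing.** This is an unadjusted two-sided comparison at d = 0.3 and 140 per arm, at the Bonferroni level (also Holm's first step).

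- Five tests: alpha = .05/5 = .01, power = Φ(2.510 − 2.576) = 47%, N for 80% power = 520.
- Fifteen tests: alpha = .05/15 = .0033, power = Φ(2.510 − 2.935) = 34%, N = 634.
- One named test: alpha stays at .05 and N does not rise on this account.

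**The case against.** The strongest reply has four parts.

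- **The article is condensed.** A multiplicity procedure or decision rule commonly sits in an analysis plan that is not shown. That would dispose of a complaint about mere absence. It does not dispose of this one: the article states the level for main-effects and growth-curve analyses and states where stricter levels apply. A plan that adjusted the primary tests would move away from that text.
- **The level is given for most analyses, not all.** This stands. A reader might infer that .05 is fixed for every primary test, and the wording does not go that far. It names no exception for the primary outcomes either.
- **The questions differ.** Post-treatment level, speed of change and follow-up are posed separately, and ITT and per-protocol are given different questions. Pooling everything into one family is a choice. This stands, and it is why the main figures use one stage and one analysis set.
- **No rule says that any single significant outcome counts as success.** This also stands. The error rates are conditional on that reading, which the article neither adopts nor rules out.

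A stronger reading is tempting: that a false claim for MATCH is more likely than not, from the 54% figure. The documents do not support it. That figure counts errors in both directions, needs all 15 tests, and needs independence. Overlapping problem scales on the same children, often from the same informant, are not independent. The count of 15 is not stated anywhere and includes BFS totals and a conditionally administered child CATS.

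**Conclusion.** The point holds at moderate size. With 12 to 15 comparisons and assumed common correlations of 0.7 to 0.3, the chance of at least one false positive is about 23–46% in either direction. Favouring MATCH it is about 12–23%, against a nominal 2.5% for one two-sided test. At a correlation of 0.9 the latter falls to about 7%. On the most lenient count, one test for each of the five listed outcomes, the rates at 0.7 to 0.3 are about 15–21% and 7–11%.

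This rests on three assumptions: the correlations, which the article does not give; the reading that any one significant primary result may be claimed as success; and .05 applying to the primary comparisons, as the text says for most analyses. A reader might infer that a false claim for MATCH is probable; a substantial chance is all that the figures show.

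**What to change.** Before any outcome is compared by arm, amend the Primary outcomes and Level of significance sections to:

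1. Name one deciding primary test by outcome, informant, scale and time point, in the ITT set at .05, and state whether it is one- or two-sided. A parent CBCL score already collected is one option; the choice is the sponsor's.
2. List the remaining outcomes as key secondary, tested with Holm or in a fixed order.
3. Label per-protocol and follow-up results as supportive.

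If the sponsor prefers to keep several primaries, apply Holm across them and restate the power in the sample size section at the adjusted level.

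The cost is protocol and registry wording, and fewer results that can be called confirmatory. No new data collection is needed. Naming one test needs no larger sample on this account, whereas keeping several primaries would cost power, as the working shows.

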### Sample size

#### The number of subjects planned to be enrolled

We plan to recruit 280 children and their families. Based on a power analysis for the analysis of main effect, we concluded that a sample size of 280 will detect an effect size of 0.3, provided power of .80, at an alpha level of .05.

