### Aims

The aims of the current trial are:To evaluate the effectiveness of MATCH therapy on children and families referred to, and treated in, Norwegian child and adolescent mental health outpatient clinics
*Specific research questions for the first aim are:*
Will children in families receiving MATCH exhibit lower levels of internalizing and externalizing problems at post-treatment compared to children in families who receive TAU, as measured by the Child Behavior Checklist (CBCL), Youth Self-report (YSR), and Child and Adolescent Trauma Screen (CATS)?Will MATCH produce faster improvements in these domains than TAU and thus be more efficient (and cost-effective) than TAU, as measured by the Top Problem Assessment (TPA) and Behavior and Feelings Survey (BFS) across weekly assessments during treatment?Will children in families receiving MATCH exhibit lower levels of internalizing and externalizing problems at follow-up (1 year after post-treatment assessment) compared to children in families receiving TAU, as measured by the CBCL, YSR, and CATS?
To implement an empirically supported treatment (MATCH) in child and adolescent mental health outpatient clinics in Norway and to assess replicability of the findings from the research on MATCH in the USTo evaluate whether potential treatment effects are associated with implementation quality and other moderators (e.g., age, gender, diagnosis, possible combinations of mental health problems)

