### Measures

Questionnaires and interviews are administered to the families in six waves, in addition to the weekly PATH questionnaire which is filled out by children (above the age of 8 years), parents and MATCH therapists between each session throughout the course of treatment. Therapists, supervisors, and team-leaders at each clinic also fill out questionnaires. See Fig. 1 and the description of measures for details. The pre-assessement (T1) is administered after receipt of consent and prior to randomization. At 3 and 6 months (T2 and T3, respectively) into treatment, a short assessment is administered to children and parents, and these are both time-invariant and thus occur at the same time for all families enrolled, regardless of group assignment or treatment progress. Shortly after treatment has concluded, families fill out the post-assessment (T4). The time at which the post-assessment is administered varies among families depending on how long the treatment period has lasted, and so this assessment is time-varying. At 15 months (T5) after treatment initiation, another short assessment is administered. The last assessment (T6), the follow-up, is administered 1 year after the end of treatment, and so is time-variant relating to T1 (because it depends on how long treatment lasted), but is time-invariant in relation to T4 (because it is carried out 1 year post treatment conclusion)

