#### For main effects

The time-variant assessments, that is, the pre-, post-, and follow-up assessments, will be analyzed using descriptive statistics and general linear models (GLM), controlling for age, gender, type of problem area, and family background information (e.g., SES).

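### The 80% power for an effect of 0.3 with 280 children holds only for a one-sided test or an unstated covariate gain; two-sided and unadjusted it is 71%

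*Protocol article*

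**What the plan says.** Under 'The number of subjects planned to be enrolled', the protocol article says "We plan to recruit 280 children and their families". From a power analysis for the main effect it concludes that "a sample size of 280 will detect an effect size of 0.3, provided power of .80, at an alpha level of .05". Allocation is equal, "with each participant having a 50% chance of being assigned to either group" ('Design and power'), so the plan implies 140 per arm.

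The section 'Level of significance to be used' says that in most analyses "a significance level of α = .05 will be used for main effects analyses", again without saying one- or two-sided. The research question in 'Aims' is worded in one direction: "Will children in families receiving MATCH exhibit lower levels of internalizing and externalizing problems at post-treatment".

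'For main effects' plans general linear models of the pre-, post- and follow-up assessments, "controlling for age, gender, type of problem area, and family background information (e.g., SES" and similar variables. The T1 score is among the data analysed, but the list of covariates does not name it. No covariate-outcome correlation is given.

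Two further sections bear on the number analysed. 'The number of participants projected at each site' expects six or more cases from each MATCH therapist. 'The selection of participants to be included in the analyses' plans an intention-to-treat analysis and also a per-protocol analysis limited to families who went through treatment. The article gives no loss rate and no intraclass correlation (ICC).

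**The concern.** An alpha of .05 stated without qualification is normally read as two-sided. On that reading, 280 children in two equal arms do not give 80% power for a standardised difference of 0.30 unless a covariate explains part of the outcome variance. A reader who takes the sentence at face value will credit the trial with more power at 0.30 than a two-sided unadjusted test has. This is the article's only justification of its sample size, so the result will be judged against it.

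**Working it through.** **Inputs.** Total 280, effect size 0.3, power .80 and alpha .05 come from 'The number of subjects planned to be enrolled'. The 1:1 allocation comes from 'Design and power'. The effect-size measure is not named; I read it as a standardised mean difference d with SD 1.

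**Formulas** (normal approximation, n per arm):
- Power = Φ(d·√(n/2) − z), with z = 1.960 two-sided or 1.645 one-sided.
- n for 80% power = 2(z + 0.842)²/d².
- With a covariate correlated r with the outcome, replace the SD of 1 by √(1 − r²).

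**Reproducing the plan's figure.** At n = 140, d·√(n/2) = 0.30 × √70 = 2.510.

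| Reading | Power at 280 | Children needed for 80% |
|---|---|---|
| One-sided .05, unadjusted | Φ(2.510 − 1.645) = 0.807 | 2 × 138 = 276 |
| Two-sided .05, unadjusted | Φ(2.510 − 1.960) = 0.709 | 2 × 175 = 350 |
| Two-sided .05, r = 0.45 (SD 0.893) | Φ(2.811 − 1.960) = 0.803 | 2 × 140 = 280 |
| Two-sided .05, r = 0.50 (SD 0.866) | Φ(2.898 − 1.960) = 0.826 | 262 |

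The t distribution gives 0.805 one-sided (278 needed) and 0.706 two-sided (352 needed), so the approximation is not the cause of the gap. Two other readings do not match .80: 280 per arm gives 0.944, and taking 0.3 as Cohen's f (d = 0.6) gives 0.999.

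Two-sided and unadjusted, the effect detectable with 80% power is (1.960 + 0.842) × √(2/140) = 0.335. The correlation at which 280 gives 80% two-sided is √(1 − 140/174.4) = 0.444, or about 0.45.

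**Margin for loss and clustering.** The article gives no loss rate or ICC, so the values here are assumptions. A 15% loss leaves 0.85 × 140 = 119 per arm. An ICC of 0.05 with six cases per therapist in both arms gives a design effect of 1 + 5 × 0.05 = 1.25, so the effective number is 140/1.25 = 112 per arm. Applying both gives 119/1.25 = 95.2.

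| Assumption | Two-sided, unadjusted | One-sided | Two-sided, r = 0.45 |
|---|---|---|---|
| Neither | 0.71 | 0.81 | 0.80 |
| 15% loss | 0.64 | 0.75 | 0.74 |
| ICC 0.05 | 0.61 | 0.73 | 0.71 |
| Both | 0.54 | 0.66 | 0.64 |

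Smaller assumptions also matter. Two-sided and unadjusted, 10% loss gives 0.66, and an ICC of 0.01 or 0.02 gives 0.69 or 0.67. If clustering at ICC 0.05 is confined to the MATCH arm (112 against 140), power is 0.66 rather than 0.61.

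**The case against.** The strongest reply is that the article nowhere says the test is two-sided and that its figure reproduces one-sided. A reader might infer that the sponsor made an arithmetic error, or that the design cannot deliver 80%. The document does not support either inference. Sidedness is simply not stated. The directional wording in 'Aims' is compatible with a one-sided test, although it does not fix one.

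The planned main-effect analysis is also not an unadjusted comparison. It is a covariate-adjusted linear model of data that include the pre-assessment. If the T1 score enters as a covariate and correlates about 0.45 or more with the outcome, two-sided power reaches 80% before loss and clustering. This stands, and it makes 71% a conditional reference figure. However, the article names neither that covariate role nor any correlation.

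The loss and ICC values are mine, and a condensed article may leave such inputs to the full protocol. The expectation of six cases applies to MATCH therapists; the article matches the number of TAU cases but not the number per TAU therapist. A post-assessment is planned when a MATCH treatment is terminated, so stopping treatment need not mean lost data. These points limit what can be said about the size of the shortfall, but not its direction.

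A reader might also infer that the 280 is claimed for outcomes that not every child provides. The weekly PATH form, for example, is "filled out by children (above the age of 8 years), parents and MATCH therapists". The sample-size statement is not tied to any child-report outcome or to CATS, so I do not press this. Nor can it be said that a null result would be misread: significant effects reported from the earlier US trials run from .38 to .70, and at 0.38 the two-sided unadjusted power with 280 is about 0.89.

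**Conclusion.** The point holds in conditional form. For a two-sided unadjusted comparison of 140 with 140 at .05, power at 0.30 is 0.71, the effect detectable with 80% power is 0.335, and 350 children would be needed. The stated 80% requires either a one-sided test (276 needed, power 0.81) or a covariate-outcome correlation of about 0.45, and the article states neither.

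Both of those readings use up the full 280. That is the number recruited, with no margin shown for loss, for the per-protocol restriction or for children who share a therapist. The direction of these effects is certain, because loss and positive within-therapist correlation both lower power. Their size is not known, and the figures above rest on the assumed 15% loss and ICC of 0.05. All figures take 0.3 as a standardised mean difference.

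**What to change.** Keep the sample size at 280 and make three changes:

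- In 'Level of significance to be used' and 'The number of subjects planned to be enrolled', declare the main-effect test two-sided at .05. If a one-sided test was intended, say so in both places.
- In 'For main effects', name the T1 score of the outcome as a covariate.
- Restate the power for that analysis. Name the outcome and effect-size measure, and give the assumed T1 correlation, therapist ICC and loss. Quote the two-sided unadjusted reference alongside: 71% for 0.30, or 80% for 0.335.

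As an example, with an assumed r = 0.5 and a design effect of 1.25, the effective number is 112 per arm and the residual SD 0.866. Power at 0.30 is then Φ(0.30 × √56/0.866 − 1.960) = 0.74 before loss.

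The cost is wording, and the stated power is likely to be less favourable. No extra children are needed.
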